### *Inclusion criteria*

- Eligible patients, aged 18 to 65 years, with a current diagnosis of mild to severe asthma will be recruited.
  - Asthma diagnosis will be made upon one of the following criteria (3):
    - FEV1 increases by at least 12% after the use of a bronchodilator (and a minimum  $\geq 200$  mL);
    - Current asthma symptoms and a positive methacholine challenge test (20% fall in FEV1 after inhalation of a provocative dose of methacholine 16 mg/mL);
    - A respirologist's current diagnosis of asthma found in the patient's medical report.
- Severity of asthma will be assessed according to prescribed pharmacotherapy, as suggested by current guidelines (1;32):
  - Patients with mild asthma using SABA as well as low doses ( $\leq 250$  mcg/day beclomethasone or equivalent) of inhaled glucocorticosteroids;
  - Patients with moderate asthma using SABA as well as low to moderate doses ( $250 \text{ mcg/day} < \text{dose} \leq 500$  mcg/day beclomethasone or equivalent) of inhaled glucocorticosteroids, with or without additional therapy (LABA or LTRA);
  - Patients with severe asthma using high doses ( $> 500$  mcg/day beclomethasone or equivalent) of inhaled glucocorticosteroids, and additional pharmacotherapy (LABA, LTRA, or Prednisone), and SABA.

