### *Sample size*

Since the study is a pilot, 50 patients are intended to be recruited to participate in the randomized control trial. Sample size calculations will be made during the study, based on gathered data. If feasible, more than 50 patients may be enrolled in order to get sufficient statistical power.

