### *Randomization (sequence generation)*

Using statistical software, a statistician will generate a blocked randomization list that will be used to allocate patients to either the intervention or the control group. Blocks of four will be used.

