### *Decisional conflict (primary outcome)*

Decisional conflict will be assessed through a French version of OHRI Decisional Conflict Scale (18). The questionnaire will be filled at baseline and after a 2-month follow-up. Sixteen items evaluate 5 dimensions of decisional conflict (informed, values clarity, support, uncertainty, effective decision) using a Likert scale. Patients' responses range from 0 (strongly agree) to 4 (strongly disagree). Patients' responses are summed, divided by 16, and multiplied by 25. Consequently, the decisional conflict score ranges from 0 (low decisional conflict) to 100 (high decisional conflict). A score greater than 37.5 suggests that there is a meaningful decisional conflict, but a score that is less than 25 is not associated with it (33). The variable will nevertheless be analysed as a continuous one. The reliability of the OHRI Decisional Conflict Scale (English low literacy version) has been evaluated using a Cronbach's  $\alpha$ , which value was above the 0.7 threshold (34). Test-retest coefficient also supports its reliability (35). The scale has been shown responsive to change, because it is able to detect an effect size of 0.2 to 0.3 in studies that compare an intervention group to a control group (33).

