If covariates (asthma knowledge, age, body mass index, atopy, environmental triggers, and respiratory tract infections) are not distributed evenly between groups, we will adjust for them in analyses. Predictors of health outcomes will be incorporated into the model as confounders if they result in a >10% change in the effect measure, following a descending procedure. Exploratory subgroup analyses according to asthma severity will be conducted since pharmacotherapy and compliance with treatments are getting more complex with the severity of the disease. Statistical interaction of body mass index will also be exploratory assessed since this covariate is hypothesized to modify the effectiveness of intervention aiming at improving asthma control (42). In addition, exploratory statistical interaction of age, education and length of the patient's meeting with the asthma nurse will be evaluated since we hypothesize that the effect measure may vary according to the level of measurement of these variables. Regarding adherence to medication, sensitivity analyses will be carried out according to different cut-offs, that will range from 60 to 80% of inhaled prescribed doses.

SAS version 9.3 (SAS Institute Inc., Cary, USA) will be used to perform the statistical analyses, using PROC GENMOD. A 2-tailed *p*-value less than 0.05 will be considered indicative of statistical significance. Since the study is a pilot, power calculation will be made *a posteriori*. Alternatively, the study size is based on the number of patients that may realistically be recruited at the IUCPQ Research Center or Outpatient Asthma Clinic according to the timeframe. Nevertheless, sample size calculations will be made during the study, based on gathered data. If feasible, more patients may be enrolled in order to get sufficient statistical power.

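### Asthma severity is given subgroup analyses only: unlike for four other modifiers, the plan states no analysis that compares the effect directly between severity classes

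*Protocol*

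**What the plan says.** The Data analysis section of the protocol names five possible effect modifiers in one paragraph. For severity: "Exploratory subgroup analyses according to asthma severity will be conducted". The reason given is that treatment, and keeping to it, become more complicated as the disease becomes more severe. The following sentences use a different term for the other four: "Statistical interaction of body mass index will also be exploratory assessed", and "exploratory statistical interaction of age, education and length of the patient's meeting with the asthma nurse will be evaluated".

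The same section defines the effect of the aids as the group-by-time term. It sets one significance rule, "A 2-tailed *p*-value less than 0.05 will be considered indicative of statistical significance", with no separate rule for reading subgroup results. Severity has three classes, mild, moderate and severe (Inclusion criteria: "Severity of asthma will be assessed according to prescribed pharmacotherapy, as suggested by current guidelines"). The planned size is 50 (Sample size: "Since the study is a pilot, 50 patients are intended to be recruited to participate in the randomized control trial").

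In Annexe 1, Table 6 has columns for group, time and their interaction but none for severity, and severity is not among the covariates in Tables 2 and 3.

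**The concern.** Whether the aids work differently in mild, moderate and severe asthma is a question about the difference between class effects. Estimating the effect within each class does not test that difference. In small classes, one result below 0.05 beside another above it is a common product of chance, even when the true effect is identical throughout.

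The authors use the suitable tool for four modifiers and name a weaker one for the fifth. If severity results were read class by class, an apparent dependence on severity could reflect class size and noise. At stake is the interpretation of one exploratory analysis.

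**Working it through.** The protocol gives no power, design effect or subgroup figure, so there is nothing of its own to reproduce. The check asks how often separate class results disagree when the true effect is the same in all classes.

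**Inputs from the protocol**
- 50 patients (Sample size).
- Three severity classes (Inclusion criteria).
- Two-sided 0.05 (Data analysis).
- Two arms, "Blocks of four will be used" (Randomization, sequence generation), with no stratification by severity mentioned.

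**Assumptions**
- Allocation is 1:1, about 25 per arm. The ratio is not stated.
- There is no dropout.
- Class sizes per arm are 8/8/9, with uneven splits as a check.
- The outcome is continuous, and the group-by-time effect is treated as a difference in mean change and tested by t-test.
- d is the effect in standard deviations (SD) of that change. The only effect size in the protocol is 0.2 to 0.3, given for the responsiveness of the decisional conflict scale ("it is able to detect an effect size of 0.2 to 0.3 in studies that compare an intervention group to a control group"). It is not a design assumption, so d is varied.

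**Formulas**
- Power in class i with n per arm: p_i = P(|T| > t(0.975, 2n−2)), where T is noncentral t with noncentrality d·√(n/2).
- Mixed result, meaning at least one class significant and at least one not: P = 1 − Πp_i − Π(1 − p_i).

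**Results for 8/8/9 per arm**

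| d | Power, all 50 | Power per class | Πp_i | Π(1−p_i) | Mixed |
|---|---|---|---|---|---|
| 0 | – | 0.05, 0.05, 0.05 | 0.0001 | 0.857 | 14% |
| 0.2 | 0.107 | 0.066, 0.066, 0.068 | 0.0003 | 0.812 | 18.7% |
| 0.3 | 0.180 | 0.087, 0.087, 0.092 | 0.0007 | 0.758 | 24.2% |
| 0.5 | 0.410 | 0.154, 0.154, 0.170 | 0.0040 | 0.594 | 40.2% |
| 0.81 | 0.80 | 0.326, 0.326, 0.364 | 0.0387 | 0.289 | 67.2% |

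Worked line for d = 0.81: 0.326 × 0.326 × 0.364 = 0.0387, and 0.674 × 0.674 × 0.636 = 0.289. So 1 − 0.0387 − 0.289 = 0.672.

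**Other splits.** With 4/8/13, 5/15/5 and 12/8/5 per arm, the mixed rate stays at 19% (d = 0.2) and 24% (d = 0.3), and is 40–41% at d = 0.5. With 10/10/5 and 6/13/6 at d = 0.81 it is 68% and 69%.

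**Simulation** (4,000 runs per scenario; splits 8/8/9 and 4/8/13; d from 0 to 0.8). The mixed rates agree with the formula. A 2-df test of effect by severity rejects in 4.4% to 5.8% of runs. At d = 0.5 the class estimates do not all have the same sign in 39–42% of runs. The mean gap between the largest and smallest class estimate is about 0.82 to 0.93 SD, although the true gap is zero.

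**Limit of the interaction test.** With 8 per arm, the standard error of a class effect is √(2/8) = 0.50 SD. For the difference between two such classes it is √(0.25 + 0.25) = 0.71 SD. A 95% interval on that difference is roughly ±1.96 × 0.71 = ±1.4 SD, so only a very large difference would be detected.

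**The case against.** The strongest reply is that the protocol has one clause on severity and does not commit the error. A reader might infer that class p-values will be compared and an interaction test ruled out. The text says neither. The word linking the body mass index sentence to the severity sentence can be read as placing both in one family of effect-modification checks, and Table 6 reserves no rows for class results. A statistical analysis plan, not available here, could supply the term. This stands, and it limits the point to what is stated: a different method is named for severity, and no direct comparison is given. It does not remove the point, because the protocol did choose methods for effect modification, in adjoining sentences, and chose differently for severity.

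A second reply is that the analysis is exploratory, in a pilot, with no decision tied to it. That stands too. But the other four modifiers are equally exploratory and still get interactions.

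A third concerns size. A reader might take two-thirds as the expected rate of mixed results. That figure needs d = 0.81, which is back-solved from 80% overall power, a target the protocol never sets. A reader might also count 21 tests (three classes by seven Table 6 outcomes). The stated reason concerns compliance, so the protocol does not support extending the count to every outcome. One of the compliance measures is binary with a log link, which the t-test figures do not cover. Interactions do not remove multiplicity either.

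Finally, it might be inferred that a misleading class-specific message will reach the thesis and articles. The protocol says only that the study's conclusions will be reported there.

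**Conclusion.** The point holds in a limited form. Severity is the only one of the five modifiers for which no interaction is stated, and the plan names no analysis that directly compares the effect between severity classes.

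If class results were read side by side under one common effect, mixed significance would occur per outcome in about 14% of trials at d = 0, 19–24% at d = 0.2–0.3, 40–41% at d = 0.5 and 67–69% at d = 0.81. One interaction test would give about 5% false signals. These figures rest on assumed effect sizes, 1:1 allocation, assumed class sizes, complete data and t-tests in place of the planned generalized estimating equations. The direction is the same for every d examined.

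The documents do not show that the investigators intend to draw conclusions from within-class p-values. The primary comparison is untouched. This is a modest, worthwhile correction to an exploratory analysis.

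**What to change.** Replace the severity clause in Data analysis with wording such as: Effect modification by asthma severity will be explored, as for the other four modifiers, by a severity-by-group-by-time interaction in the full-sample model (2 df, or an ordered severity score if pre-specified). Class estimates will be shown with 95% confidence intervals, and no class-specific claim will be based on within-class significance.

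The choice between 2 df and an ordered score is open. The score uses 1 df but assumes a linear trend across classes.

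The cost is one sentence and one added interaction, with its lower-order severity terms, in a model already planned. No new data are needed. The drawback is low power at 50 patients: a non-significant interaction must not be reported as showing equal effects, and the text should say so.

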### **Developing prototypes of shared decision making aids**

The aids will be designed in order to present a brief description of asthma and a summary of the current guidelines regarding asthma management. In addition, they will provide evidence-based information, such as probabilities of risks, benefits, and uncertainties associated with each treatment option, whenever possible (24). The aids will be designed in order to help patients clarify and express what matters the most to them, and to guide and facilitate discussion and communication of facts and values between patients and caregivers (24;27).

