### **Evaluation of the aids**

In order to recruit patients with mild to severe asthma in the study, medical reports of patients attending the IUCPQ Outpatient Asthma Clinic or having participated in studies at the Research

Center will be screened by the study coordinator. Patients who will meet the eligibility criteria (see *Inclusion criteria* below) will be contacted by the asthma nurse at the Outpatient Asthma Clinic prior to their meeting with her, or by the study coordinator if patients are recruited at the research center. Relevant information on the study objectives will be given by the study coordinator to eligible patients who will be interested to participate in the study. Those who will agree to participate in the study will sign an informed consent. The study will have been approved by the institutional ethics committee. Patients who will have given feedback on the aids in step 2 will not be enrolled, according to the IPDAS criteria.

The baseline visit (visit 1A) will take place at the IUCPQ Research Center and Outpatient Asthma Clinic. With the help of the study coordinator/asthma nurse, asthma control will be assessed, using the Asthma Control Scoring System (30). The study coordinator will evaluate patients' compliance with pharmacotherapy, using the Compliance Interview Questionnaire. In addition, the Decisional Conflict Scale (18) and the Asthma Knowledge Questionnaire (31) will be filled by patients. In order to control for covariates, if relevant, data on enrolled patients' health (age, height, weight, atopy, respiratory tract infections) and environmental factors will be gathered by the study coordinator, using the IUCPQ Asthma Consultation Form. For the same reason, enrolled patients' data on asthma knowledge at baseline will also be used. Visit 1A should last about 45 minutes.

After having filled the questionnaires, the study coordinator will give patients sealed envelopes in order to randomize them in the intervention or control group (see *Randomization (sequence concealment)* below). Consequently, patients will get, or not, the shared decision making aids, depending on the group they belong to (visit 1B). Those who will belong to the experimental group will have to pass through the steps of the aids before meeting the asthma nurse. Those belonging to the control group will skip this stage and therefore will meet the nurse directly, as in usual care. In both groups, there will be one meeting with the nurse per patient.

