### ***Shared decision making aids***

The shared decision making aids that will be used in the intervention group will be the latest version of those developed in the previous stage of this study (developing shared decision making aids). Patients in the experimental group will receive the aids and will be asked to go through them prior to their meeting with the asthma education nurse at the IUCPQ Outpatient Asthma Clinic. During this meeting, the asthma nurse will review patient's written action plan. Individualized education and counselling will also be provided. The length of the meeting will be evaluated.

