### *Predictors of Asthma Control (Covariates)*

Age (in years) and body mass index for adults ( $\text{weight (kg)} / [\text{height (m)}]^2$  or  $\text{weight (lb)} / [\text{height (in)}]^2 \times 703$ ) will be assessed. In addition, inflammatory factors associated with asthma control will be measured. These factors are atopy (self-reported allergy; self-reported exposure to allergen), environmental triggers (smoking or exposure to second hand smoke), and respiratory tract infections in the last month. All those will be assessed through the IUCPQ Asthma Consultation Form. Covariate measurements will be undertaken at baseline. Questions regarding respiratory tract infections in the last month will also be asked after a 2-month follow-up. Factors associated with asthma control will be modeled as continuous or categorical variables.

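### Nurse-visit length, measured after randomisation, is planned as an exploratory effect modifier, and the text leaves open adjustment for 2-month respiratory infection (minor)

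*Protocol*

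**What the plan says.** **Nurse-visit length.** In Data analysis, after subgroups by severity and an interaction with body mass index, the protocol states that "exploratory statistical interaction of age, education and length of the patient's meeting with the asthma nurse will be evaluated". The same sentence goes on to give the reason: "meeting with the asthma nurse will be evaluated since we hypothesize that the effect measure may vary according to the level of measurement". Under Shared decision making aids it says of the visit: "The length of the meeting will be evaluated". The Usual care section says the same for the control arm.

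The order of events is in Evaluation of the aids. After the baseline questionnaires the patient receives the sealed envelope. Aid-arm patients "have to pass through the steps of the aids before meeting the asthma nurse". For the other arm: "Those belonging to the control group will skip this stage and therefore will meet the nurse directly, as in usual care". The section on developing prototypes gives, as one design aim of the aids, "to guide and facilitate discussion and communication of facts and values between patients and caregivers".

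**Respiratory infection.** Data analysis names infection among the covariates and says that if these "are not distributed evenly between groups, we will adjust for them in analyses". A second trigger admits predictors that change the effect measure by more than 10%. The section Predictors of Asthma Control (Covariates) places covariate measurement at baseline, then adds: "Questions regarding respiratory tract infections in the last month will also be asked after a 2-month follow-up". In Annexe 1, Table 2 marks infection at both baseline and 2 months, the only covariate so marked. Table 3, which compares covariates between arms, is a baseline table and includes infection.

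**The concern.** An effect modifier is interpretable in a randomised trial when it is fixed before allocation: within each level, the two arms are still randomised groups. Age and education meet that condition. Visit length does not, because it is observed after allocation and after the aid may have acted on the conversation. Patients with visits of equal length in the two arms may differ in ways that matter for outcome, so an apparent variation of effect by length could reflect who has long visits in each arm.

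Infection raises a related question. The 2-month item looks back one month from visit 2, so it falls wholly within follow-up. If that value entered an adjusted model and the aids had changed infection, adjustment would remove part of the effect and could add bias through factors that drive both infection and asthma control.

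At stake are an exploratory statement about visit length and, conditionally, the adjusted asthma control estimate.

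**Working it through.** There is no stated figure to reproduce: the protocol gives no effect size, standard deviation or correlation for these variables. The check is first one of timing, then of size under stated assumptions.

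**1. Timing and role of visit length.** The sequence is baseline questionnaires, envelope, aid (one arm only), nurse visit, length recorded. Length is therefore post-randomisation in both arms and post-intervention in the aid arm. It is not on the covariate list. The main model in Data analysis and Table 6 contains group, time and their interaction, with no term for length. The problem is confined to the exploratory interaction.

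**2. Which infection value is adjusted for.**
- Pointing to baseline: the general timing rule in the covariate section, and Table 3.
- Pointing to either visit: the repeat question at follow-up, and the two marks in Table 2.
- Neither adjustment rule in Data analysis gives a time point.

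The text therefore permits the 2-month value without prescribing it.

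**3. Illustration for visit length (all inputs assumed).** Take 25 patients per arm (50 in total, roughly 1:1), A = 1 for the aid arm, and an unmeasured prognostic factor U with unit variance. Set outcome Y = 0.5·A + 0.5·U + noise and length L = s·A + c·U + noise, each with unit variance within arm. There is no true effect modification. This uses a single follow-up outcome, which is simpler than the planned repeated-measures model.

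The within-arm slope of Y on L is 0.5·c. Hence:
- with equal c in both arms, the group term at equal length is 0.5 − 0.5·c·s;
- the fitted interaction is 0.5·(c in aid arm − c in control arm).

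With c = 0.6 in both arms: s = 0.5 gives 0.5 − 0.15 = 0.35, and s = 1 gives 0.5 − 0.30 = 0.20. With c = 0.6 in control and 0 in the aid arm, the interaction is 0.5·(0 − 0.6) = −0.30. Simulation (4,000 runs per row) agrees:

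| Shift s (SD) | c control / aid | Group term, no length | Group term, with length | Interaction | False positives at 5% |
|---|---|---|---|---|---|
| 0 | 0 / 0 | 0.50 | 0.50 | −0.01 | 5.1% |
| 0 | 0.6 / 0.6 | 0.50 | 0.50 | −0.01 | 5.1% |
| 0 | 0.6 / 0 | 0.50 | 0.50 | −0.31 | 17.6% |
| 0.5 | 0 / 0 | 0.50 | 0.50 | 0.00 | 5.2% |
| 0.5 | 0.6 / 0.6 | 0.50 | 0.35 | 0.00 | 5.3% |
| 0.5 | 0.6 / 0 | 0.50 | 0.42 | −0.30 | 17.3% |
| 1 | 0 / 0 | 0.49 | 0.50 | 0.00 | 5.2% |
| 1 | 0.6 / 0.6 | 0.50 | 0.20 | −0.01 | 4.8% |
| 1 | 0.6 / 0 | 0.50 | 0.35 | −0.30 | 16.6% |

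The model without length stays at about 0.50 throughout. A shift in length alone does not create a false interaction; that requires length to track prognosis differently in the two arms.

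**4. Illustration for 2-month infection (all inputs assumed, arbitrary outcome scale, 400,000 simulated patients).** The direct effect is 0.5 and infection costs 0.6. An unmeasured factor both raises infection risk and worsens the outcome. The total effect is about 0.5 + 0.6 × (fall in infection risk).

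| Infection, control → aid | Total effect | After adjustment |
|---|---|---|
| 27% → 27% | 0.50 | 0.50 |
| 27% → 19% | 0.54 | 0.46 |
| 27% → 13% | 0.58 | 0.44 |

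Arithmetic check, last row: 0.5 + 0.6 × (0.271 − 0.132) = 0.583, against 0.580 simulated. The adjusted values fall below even the direct effect of 0.50, because infection shares the unmeasured factor with the outcome.

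**The case against.** The strongest reply is that little depends on either item. The length interaction is labelled exploratory, sits outside the main model, and may prove harmless: the nurse is described as doing the same things in both arms, and the protocol says nothing about the aids lengthening or shortening the visit. For infection, the baseline rule and Table 3 are the natural reading of the imbalance clause. The protocol treats infection as something that worsens symptoms, and nowhere says that the aids or better controller use would reduce it. The illustrations depend on chosen inputs, and several choices show no distortion.

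Much of this stands, and it limits the point. Three stronger readings should be set aside.

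- A reader might infer that the randomised comparison is broken. It is not: the main group-by-time estimate contains no length term.
- A reader might infer that the protocol adjusts for 2-month infection. It does not say so; it leaves the time point open.
- A reader might infer that infection is the only listed covariate able to move the group-by-time term. That holds only with complete data and an identity link. The Bias section anticipates loss to follow-up, and binary compliance has a log link.

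The exploratory label does not answer the remaining issue. It lowers the weight of the result but does not make length a baseline variable, and the protocol groups it with age and education without distinction. The baseline rule does not settle infection either, because Table 2 lists the 2-month value as a covariate.

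**Conclusion.** The point holds in limited form and is minor. The visit-length part is firm on timing: length is recorded after allocation and, in one arm, after use of an aid meant to shape the discussion, so effects by length would not be randomised comparisons. Whether they would mislead depends on whether length tracks prognosis and whether the aids alter length or that link. Over the assumed range, false-positive interactions run from about 5% to about 18%, and the group term in a model containing length from 0.50 down to 0.20.

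The infection part is an ambiguity. It causes bias only if the 2-month value is used and the aids affect infection, neither of which the protocol states. Over the assumed range, the loss on adjustment runs from nothing to 0.58 − 0.44 = 0.14. None of these figures estimates what this trial would show.

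**What to change.** In Data analysis, remove nurse-visit length from the exploratory effect modifiers, keep the baseline ones (age, education, body mass index), and report length by arm as a process outcome. If an analysis involving length is still wanted, label it non-randomised and mediation-type. State in the same section that only the baseline infection value may enter adjusted models, with 2-month infection reported descriptively or in a labelled sensitivity analysis. Align Table 2 so that the 2-month infection item is no longer shown as an adjustment covariate.

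The cost is a few sentences, one table edit and the loss of one exploratory analysis. Data collection does not change, since length is already to be recorded in both arms and infection at both visits.
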